## Abstract

Research shows that exercise training programmes lead to several improvements in older adults’ health-related quality of life (HRQoL) and well-being. This study will examine the effects of an active retirement programme on Portuguese older adults, investigating its effects on body composition, physical fitness, HRQoL, and physical activity level (PAL). Therefore, a parallel-group randomised controlled trial will be conducted, including body composition (height and body weight), physical fitness (strength, flexibility, agility, postural control, and gait), HRQoL, and PAL assessments before and after the application of the programme. The programme will be carried out for six months, two days per week (45 min), plus a year of follow-up. The programme will consist of six circuits with eight physical exercises each. The circuits will change at the end of the four weeks (one monthly circuit). The exercises’ difficulty will increase throughout the programme, with alternatives for all the participants. If the effectiveness of the programme is demonstrated, implementation in different services and municipalities could be advised, as the actors involved in health and social services should promote the well-being of their citizens through, among others, health-related physical activity and the prevention of diseases associated with inactivity.

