Research on how PA affects health-related quality of life (HRQoL) has shown that PA’s benefits regarding quality of life were limited [22,23]. Several studies have evaluated the sensorimotor system in the elderly and obtained strength, mobility, and balance improvements, but these results were not consistent due to the reduced sample [20,21], being short-term (12 weeks or less), or only assessing some abilities [17]. This study will last 24 weeks, and its effects will be measured through gait, postural control, strength, flexibility, balance, and agility. Hence, this study will aim to (1) assess the effectiveness of an active retirement programme on elderly body composition, physical fitness, HRQol, and PAL and (2) assess the programme’s effectiveness throughout the ageing process (follow-up).

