### 2.3. Sample Size

Sample size calculations were performed using the G*Power 3.1.9.4 software (Kiel University, Kiel, Germany), selecting the statistical test to compare the difference between two independent means (two groups). Thus, accepting an alpha risk of 0.05 and a beta risk of 0.2 in a bilateral contrast and assuming a moderate effect size of 0.5, a total of 160 participants (80 subjects in the experimental group and 80 in the control group) were sufficient to reach a minimum potency of 90%.

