### 2.7. Measures

A variety of tools will be used. All measures will be undertaken at baseline, at the end of the intervention, and one year after the end of the intervention (follow-up). Before the first measurement, all participants will go through a familiarisation phase to familiarise themselves with the different instruments and assessments included in this project.

a. Anthropometrics and body composition. Bodyweight and height will be assessed. Before the measurements, participants will be asked to remove their shoes, socks, and heavy clothing (coats, sweaters, coats, etc.). They will also be asked to empty their pockets and remove belts and other accessories (bands, pendants, etc.). Height will be measured using a stadiometer (Seca 22, Hamburg, Germany). This instrument must be placed on a vertical surface with the measuring scale perpendicular to the ground. Participants will be positioned in a standing position, with their shoulders balanced, and their arms relaxed along their body. Height will be taken in cm and rounded to the nearest mm. Body weight will be measured using a scale. Body weight will be recorded in kg. and the body mass index (BMI) will be determined using the formula: weight × height^2^.

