### 2.8. Statistical Analysis

Descriptive statistics and computations will be performed with SPSS (version 25.0; IBM SPSS Inc., Armonk, IL, USA). Personal data will be kept anonymous.

The normality and homogeneity of data will be checked by applying Kolmogorov– Smirnov and Levene’s tests, respectively. Data will be presented as means and standard deviation (SD) (parametric variables) or median and interquartile range (IR) (nonparametric variables). The independent samples t-test (parametric variables) or the Mann–Whitney U test (non-parametric variables) will be used to determine whether the experimental and control groups were comparable at baseline in terms of participant characteristics. Then, repeated measures of ANCOVA will be applied to analyse the intervention effects on the different dependent variables, adjusted by age and baseline outcomes. Cohen’s d (with a 95% confidence interval) will also be included in the results as the effect size. Effect size thresholds will be interpreted as follows: >0.2, small; >0.5, moderate; >0.8, large [36]. Statistical significance will be computed for the effect of time and the interaction group × time. The alpha level will be fixed at *p* ≤ 0.05.

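### No primary outcome or time point is named, so the effectiveness claim draws on at least 21 between-group scores, each tested at 0.05, with a false-positive chance several times the nominal rate

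*Protocol article*

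**What the plan says.** The Introduction gives the first aim as to "assess the effectiveness of an active retirement programme on elderly body composition, physical fitness, HRQol, and PAL". The four domains stand as equals, and each except PAL contains several scores.

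Section 2.3 sizes the trial for a comparison of two independent means, "assuming a moderate effect size of 0.5", with 80 participants per group. It does not say which mean.

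Section 2.8 states that "repeated measures of ANCOVA will be applied to analyse the intervention effects on the different dependent variables", with adjustment for age and baseline. It adds: "Statistical significance will be computed for the effect of time and the interaction group" × time. "The alpha level will be fixed at" p ≤ 0.05. It gives no order among the outcomes and no adjustment. It does commit to reporting Cohen's d with a 95% confidence interval.

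The Abstract attaches a consequence: "If the effectiveness of the programme is demonstrated, implementation in different services and municipalities could be advised". The article does not say what would count as demonstrating effectiveness.

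**The concern.** A sample size and an alpha level both refer to a hypothesis, and this article does not identify one. The power statement therefore applies to no particular outcome, and the 0.05 protects each test separately but not the conclusion that the programme works.

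The rest of the article does not supply an implied primary outcome. The Discussion describes the trial as testing effects on HRQoL and fall prevention. The Conclusions drop PAL and add fall risk, which is not among the measures in section 2.7. The time point is also open: section 2.1 places assessments at baseline and after the intervention, while section 2.7 adds one a year later.

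At stake is a possible recommendation to extend the programme to services and municipalities. With no outcome designated in advance, whichever score turns out significant could be put forward as the evidence.

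**Working it through.** **1. The plan's own figure.** Inputs from section 2.3: 80 per group, d = 0.5, two-sided alpha 0.05.

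- Normal approximation: 0.5 × √(80/2) − 1.96 = 3.162 − 1.960 = 1.202, which gives power 88.5%.
- Noncentral t: 88.2%.

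This is close to the stated minimum of 90%, though slightly below it; 90% would need 85 (normal) or 86 (t) per group. Section 2.3 also gives a beta of 0.2, which is 80% power and needs only 63 or 64 per group. Those two statements should be reconciled, but that is a separate matter. Here, 88% is the power for one outcome tested once at 0.05.

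**2. Number of between-group scores (section 2.7).**

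| Domain | Scores |
|---|---|
| Body composition: weight and BMI (height not counted) | 2 |
| Physical fitness: items I to VIII | 8 |
| SF-36: eight dimensions and two summary components | 10 |
| IPAQ-SF | 1 |
| Total | 21 |

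This is a minimum. Gait has a natural and a paced condition, and IPAQ-SF sitting time could be a further score. Exertion, adherence and enjoyment relate to the exercise sessions and are left out. The test of time is also left out, because it does not compare the groups; only group × time does.

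**3. No effect, independent scores.**

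- Either direction: 1 − 0.95^21 = 65.9%.
- In the programme's favour: 1 − 0.975^21 = 41.2%.

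**4. No effect, correlated scores.** The article gives no correlations, so these are assumptions. Multivariate normal simulation, 300,000 draws, 21 scores with a common correlation:

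| Correlation | Either direction | In favour |
|---|---|---|
| 0.1 | 64% | 37% |
| 0.3 | 55% | 29% |
| 0.5 | 43% | 22% |
| 0.7 | 30% | 15% |

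Block structures (fitness 0.2–0.5, SF-36 0.4–0.7, between domains 0.1–0.3) give 44–59% in either direction and 23–32% in favour.

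**5. Against the nominal rates.** At correlation 0.7, 30/5 = 6 times in either direction and 15/2.5 = 6 times in favour. At 0.1, 64/5 is about 13 times and 37/2.5 about 15 times.

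**6. Two ways to restore control.**

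- One primary outcome at 0.05: false-positive risk 5% (2.5% in favour), power still about 88% at d = 0.5.
- Bonferroni over all 21: 0.05/21 = 0.00238 per test, familywise error at most 5%, but power per outcome falls to 53% (t) or 55% (normal).

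**The case against.** A reader might infer that a programme with no effect would probably be declared effective on something. The figures do not support that. A programme is declared effective only on a result in its favour, and that chance does not reach 50% in any case computed: 41% if the scores were independent, 15–37% at the assumed correlations. The 66% counts results in either direction and needs independence, which cannot hold. BMI is computed from weight, the SF-36 components summarise its dimensions, and the two sway tests are the same test under two conditions.

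Nor does the article state that one significant score out of 21 is enough. The Abstract says only that roll-out could be advised, and the aim is set out by domain. The supportable criticism is that no success rule is given. It would also be wrong to double the count because section 2.8 reports two p-values per outcome.

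A multiplicity procedure may sit in an analysis plan that is not shown, so its absence here is not held against the article. The trial is registered, and the registration may name a primary outcome. The planned confidence intervals for Cohen's d are useful, although they do not control error.

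What survives is the lack of a primary outcome. That defines the trial's question and gives the sample size its meaning, and it is not normally left to an analysis plan. This article has a full sample-size paragraph, a full outcome list and an explicit alpha, yet leaves the primary outcome unstated.

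**Conclusion.** The concern holds in this form: the article names no primary outcome or time point, its power statement refers to no identifiable hypothesis, and its effectiveness conclusion has no controlled false-positive rate. With 21 group × time tests at 0.05 and no true effect, the chance of at least one false-positive result is at most about 66% in either direction (41% in favour), and about 30–64% (15–37% in favour) at common correlations of 0.7 to 0.1.

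These figures assume 21 scores, one two-sided comparison per score with an approximately normal statistic, and correlations that the documents do not give. The 41% is an upper limit provided the scores, all oriented towards benefit, are not negatively correlated. If more scores or time points are tested, the chance rises. The size is uncertain, but in every scenario above it is several times the nominal rate.

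**What to change.** Before any unblinded data are seen:

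- Name one primary outcome at one time point as the sole basis for the effectiveness claim. If the registration already names one, carry that over.
- State in section 2.3 that d = 0.5 refers to that outcome and time point.
- Report the remaining scores as secondary, either as estimates with 95% confidence intervals and no effectiveness claim, or with Holm-adjusted p-values.

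This changes wording only and needs no additional participants: 80 per group keeps about 88% power at d = 0.5 for the named outcome. The cost is that an isolated secondary result can no longer carry the conclusion, and the investigators must choose which outcome matters most.

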## 3. Discussion

This project will be the first conducted developing a sensorimotor training programme for 24 weeks using different sensorimotor skills in Portuguese older adults, to test this programme’s effects on HRQoL and fall prevention compared to usual care. Different difficulty levels will be included, facilitating individualisation. This training programme can be applied by multiple agents who might be interested in reaping the benefits of these types of activities, since this training method does not require any specific installation and can be completed indoors or outdoors.

In this sense, Avelar et al. [21] carried out a similar quasi-experimental study, with a similar training period composed of exercise circuits to improve strength, gait, functional reach, and static and dynamic balance, among others. Positive responses in lower limb strength, power, mobility, and static and dynamic balance were found, although the sample was small [20,21,27], compared to the 160 participants expected for our study. Other research [17,18,39] used sensorimotor training programmes on functional capacity and balance for a short time, from two to six weeks. Despite the short period, positive results were obtained concerning balance, mobility, activities of daily living performance, and fall risk. Thus, by improving physical capabilities, fall risk could be lower. Other studies [19,20,21] have applied 12–13 weeks of sensorimotor training, half of what is proposed in this protocol. There were positive results for mobility and balance and an improved ability to produce the maximum and explosive force of leg extensors. Several of these studies developed a short-time practical application [39], had a small size [21], or assessed only one or two sensorimotor abilities [17,18,19,20]. For all these reasons, no studies with consistent results have produced an advance on this topic, bearing in mind that the percentage of old people practising PA is very low [40], so it is essential to promote PA practise, as sensorimotor skills may be deficient.

The application of this study is expected to obtain an increase in physical capacities such as strength, flexibility, gait, postural control, balance, and agility. In addition, we are also aiming to improve the participants’ HRQoL and reduce their fall risk. The programme could be applied to public and private entities. In the public sector, the application of active retirement programmes within the services offered by public health programmes exists at a regional level, as is the case of the “Alma Senior” programme, developed in the Municipality of Almada, Portugal, or the “The Exercise Looks After You” programme, developed in Extremadura, Spain, which increases its cost–benefit ratio for all aspects related to HRQoL and fall prevention in this sector. Likewise, the possibility of implementing this training system in different associations can be studied. In the private sector, a focus group study can include the heads of health and sports centres, focusing on the applicability of sensorimotor training in their centres, with the results of the study able to highlight the potential advantages of private sector application.

The Portuguese population has experienced a substantial increase in average life expectancy in the last four decades. During the same period, there has been a progressive increase in health expenditure [41]. Regarding the relationship between ageing and health expenditure, there does not seem to be a consensus in the literature on the effects of ageing on health expenditure. The literature refutes that population age is a major determinant of health expenditure and other factors, thus considering a strong positive correlation between the two variables. This correlation is not confirmed in the majority of econometric analyses that have been developed in the last two decades in the area of health economics [42]. Thus, PA should be considered an essential item for public health, since, if performed regularly, it is considered an important condition for health promotion and the prevention/remediation of chronic diseases, for different age groups [43].

Regarding limitations, one of the limitations that will exist for the application of this study is being after/during the COVID-19 pandemic. We must take extra care, by adding space and material for the hygienists, to give greater security to the programme. Travel to the space where the programme will be carried out may also be a limitation, considering that the population under study involves people who no longer travel by car; it may be too far away for them to travel on foot, so there will be increased costs due to the necessity of using public transport.

In the future, it would be interesting to evaluate all age groups, in addition to this age group, such as those who are still actively employed, to have a better perception of what happens throughout life in terms of sensorimotor behaviour, not just during the ageing process. This could result in people being able to act from an early age, to improve the capacities analysed in this study. In addition, it would be interesting to add other clinical variables more related to health, such as blood pressure and cholesterol, because, as reported in other studies [44], there were improvements in these variables in the physical condition of participants. We can also analyse the effects of the programme on the number of medical appointments. Finally, applying a pre-participation physical assessment of the participants by a sports physician would be beneficial.

The added value of this study will be the acquired knowledge about sensorimotor training for the elderly, which will present a scientific advancement for PA, HRQoL, and sedentary behaviour prevention. Finally, it will be innovative in creating an intervention manual and a digital library with specific exercises for sensorimotor training, which allow for better adaptation and motor coordination.

## 4. Conclusions

This study will investigate the effectiveness of an active retirement programme in the elderly on their body composition, physical condition, HRQoL, and fall risk, advancing the knowledge of PA, health, and wellness.

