b. Physical fitness. Participants will wear tracksuit bottoms and will be asked to remove accessories and any objects in their pockets. The following measures will be carried out (Figure 3): (I) agility and execution speed will be assessed through the Timed Up and Go (TUG) test, which consists of getting up from a chair, walking in a straight line three meters away, and walking back and sitting down again [25]; (II and III) postural control will be tested through a force platform (Ber-tec4060-Columbus; USA). The assessment will consist of measuring the oscillations in a static bipedal position, with eyes open (two minutes) and with eyes closed (two minutes) [26]; (IV) gait will be assessed using the mobile application “Phyphox” on the surface of the skin, at the inner edge of the tibia, to quantify the number of steps and time. Participants will be asked to walk a pre-established route, without slopes or obstacles, for 10 min, at their natural cadence and, later, walk the same route at a pace determined by complex stimuli (auditory metronome—loudspeakers, which allow for hearing beats that correspond to steps) [27]; (V) muscular endurance will be assessed by rising up from the chair or bending and straightening for 30 s, during which the strength of the lower limbs involving the vastus medialis obliquus (VMO) and the vastus lateralis (VL) will also be calculated [28]; (VI) upper limb strength will be determined by the number of times that a weight can be lifted by performing a flexion–extension of the arms for 30 s [28]; (VII and VIII) flexibility will be evaluated by two tests: “the sit and reach” for lower limb flexibility, where participants, from a seated position with one leg extended, will slowly bend down, sliding their hands down the extended leg until they touch (or pass) their toes [28]; and “the behind the back reach” test for upper limbs, assessing the shoulder’s full range of motion, which will consist of measuring with a ruler the distance between (or the overlap of) the middle fingers behind the back [28].

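### The Discussion and Conclusions say the trial tests fall prevention and fall risk, but no listed measure counts falls or is designated as a fall-risk measure

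*Protocol article*

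**What the plan says.** The formal aim in the Introduction is to "assess the effectiveness of an active retirement programme on elderly body composition, physical fitness, HRQol, and PAL", with a second aim on follow-up. Falls are in neither aim, and the Abstract lists no fall outcome.

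The later sections say something different. The Discussion states that the project is designed "to test this programme’s effects on HRQoL and fall prevention compared to usual care" and adds that "we are also aiming to improve the participants’ HRQoL and reduce their fall risk". The Conclusions say the study will investigate the "effectiveness of an active retirement programme in the elderly on their body composition, physical condition, HRQoL, and fall risk".

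Section 2.7 itemises the measures, a to g. The physical tests nearest to falls carry other labels: "agility and execution speed will be assessed through the Timed Up and Go (TUG) test", while the force platform is assigned to postural control. The only link drawn to falls is in the Discussion, after a summary of earlier short studies: "Thus, by improving physical capabilities, fall risk could be lower".

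For body composition, section 2.7 says "Bodyweight and height will be assessed" and derives BMI from them. The Abstract defines the term in the same way, as height and body weight.

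**The concern.** A trial can claim to have tested only what it measures. Here the statement of what is tested gains a fall outcome between the aims and the Conclusions, and no measure follows it. If the wording stands, a favourable Timed Up and Go or sway result could be read as evidence on falls although no fall was recorded. Because no measure is named in advance as the fall-risk marker, the choice among several candidates would also stay open until the results are known.

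The article gives this wording some weight. The Abstract says that wider implementation could be advised if effectiveness is shown, and the Discussion links public-sector value to fall prevention. The limitations paragraph does not mention the gap.

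**Working it through.** The plan states no figure on this point, so the check compares what is claimed with what is measured.

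**Step 1: domains claimed.**

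| Place | Domains named |
|---|---|
| Introduction, aim 1 | body composition, physical fitness, HRQoL, physical activity level |
| Discussion, opening | HRQoL, fall prevention |
| Discussion, expected results | physical capacities, HRQoL, fall risk |
| Conclusions | body composition, physical condition, HRQoL, fall risk |

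The aim and the Conclusions each name four domains. Physical activity level is replaced by fall risk.

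**Step 2: measures in section 2.7.**

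| Item | Recorded | Fall count, fall history or designated fall-risk measure? |
|---|---|---|
| a | weight, height, BMI | no |
| b | Timed Up and Go, sway, gait (steps, time), 30 s chair and arm tests, two flexibility tests | no; several bear on balance and mobility |
| c | SF-36 | no |
| d | IPAQ-SF | no |
| e | Borg exertion | no |
| f | adherence | no |
| g | PACES | no |

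The result is 0 of 7 items, and no fall-risk cut-off is given for any test in item b. Section 2.8 adds no fall endpoint.

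**Step 3: what a fall outcome could deliver if added.** The documents give no fall frequency, so these inputs are assumptions: control-arm proportion with at least one fall 20% to 40%, risk ratio 0.7 or 0.8, two-sided alpha 0.05, and 80 per arm as in section 2.3.

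| Control proportion | Risk ratio | Power at 80 per arm | Per arm for 80% power |
|---|---|---|---|
| 20% | 0.7 | 17.0% | 615 |
| 20% | 0.8 | 9.6% | 1447 |
| 30% | 0.7 | 25.5% | 367 |
| 30% | 0.8 | 13.4% | 859 |
| 40% | 0.7 | 35.9% | 244 |
| 40% | 0.8 | 18.2% | 564 |

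A count analysis would give somewhat different figures.

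**Step 4: recall periods.** With a 12-month look-back at baseline, the visits in section 2.7 would cover 12, 6 and 12 months. At a constant rate of r falls per year, the expected counts are r, 0.5r and r. Raw counts would halve and then double with no change in risk, so recall time must enter as exposure.

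**Step 5: body composition.** The change in BMI is (change in fat mass + change in lean mass) / height². If fat falls by x kg and lean mass rises by x kg, this is (−x + x) / height² = 0. BMI therefore cannot separate the two. This is true by definition and does not show that such an exchange is expected here.

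**The case against.** The strongest reply is that fall risk is not the same as falls. The trial measures Timed Up and Go, sway with eyes open and closed, gait and chair rise, all of which could serve as indirect markers, and the Discussion's link is hedged. A reader might infer from the missing fall count that the trial can say nothing relevant to fall risk. The documents do not support that reading. The gap is clear for fall prevention. For fall risk it is narrower: a surrogate is implied but never designated.

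It can also be said that the operative text is consistent. The Abstract, aims, measures and analysis plan no fall endpoint, and the wording at fault is confined to the Discussion and Conclusions. That stands. No endpoint, sample size or analysis is affected, but it does not remove the statement that fall prevention is tested.

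A reader might further infer that the body composition outcome is concealed or invalid. It is neither. The Abstract defines it openly, no fat or lean mass is promised, and effects on weight and BMI can be reported. What remains is a loose label.

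Finally, how results will be worded is a forecast. No section says that Timed Up and Go or sway results will be presented as fall prevention.

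**Conclusion.** The point holds as a mismatch between stated claims and listed measures. No effect of the programme on falls can be estimated from this design, because none of the seven measures records them. A statement on fall risk would rest on an undesignated surrogate. Effects on balance, mobility and the other measured outcomes are untouched. The conclusion assumes that section 2.7, which is detailed and itemised, lists all the outcomes. The body composition label is a minor matter of naming.

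**What to change.** **Preferred: wording only.** In the Discussion (the opening statement of purpose and the paragraph on expected results) and in the Conclusions, replace the references to fall prevention and fall risk as things tested, aimed at or investigated with the outcomes measured: Timed Up and Go, postural sway, gait and chair rise. State that any link to falls is a hypothesis. This costs a few sentences.

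**Alternative: add a fall outcome.** Ask for the self-reported number of falls at the visits in section 2.7, in identical words in both arms. Compare arms as a rate with the recall period as exposure, and label the outcome exploratory. First reconcile section 2.1, which places assessments at baseline and after the intervention, with section 2.7, which adds one at one year. The costs are one question per visit, low power, recall over as much as 12 months, and self-report by participants who know their allocation (section 2.4).

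**Labelling.** Report the body composition outcome as body weight and BMI throughout. Section 2.7 prints the BMI formula as a product of weight and squared height; this separate slip should be corrected to division at the same time.
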